### Intervention

Cogmed (RM version), is an adaptive working memory training program designed for children aged 7 years and up. The training is built into a series of interactive, computerised activities, which in this study are carried out in the child’s home. The program involves 25 training sessions carried out over a 5 to 7 week period. Each session runs for approximately 35 minutes and comprises 8 different working memory tasks. For the first 5 sessions, children train on the same games. On the 6^th^ session and every 5^th^ session thereafter, a new game is introduced, replacing 1 of the existing games. The program matches the complexity level of individual games with the child’s current working memory capacity on a session-by-session basis such that the complexity of the task increases adaptively with the child’s capacity.

A placebo, non-adaptive version of Cogmed was designed for the purpose of trial evaluations [36,39]. The placebo version again involves 25 sessions carried out over 5 to 7 weeks. Each session will also run for approximately 35 minutes and consists of 8 games. In this version, tasks are set to a low level of complexity throughout the training period to ensure the training does not tax working memory, but instead provides a control for the experience of sitting in front of a computer and engaging with tasks. This non-adaptive (placebo) version of the program will be administered to participants randomised to the placebo group.

The training period refers to the time from the first training session in the home to either the last training session (25^th^ training session) or the end of the 7^th^ week, depending on which occurs first. Both versions of the Cogmed training program are set-up by a Cogmed coach (the trial’s project co-ordinator or research assistant). Depending on whether the family has consented to neuroimaging and the availability and schedule of the family, the Cogmed start-up session will be arranged either at Murdoch Childrens Research Institute or at the family home. This flexible arrangement minimises the number of visits families need to make to the Murdoch Childrens Research Institute. If consent was not given for the neuroimaging aspect of the study, the Cogmed coach will visit the family home to conduct the Cogmed start-up session and set-up a laptop computer with the allocated training program (Cogmed or placebo). However, if neuroimaging consent was received, the Cogmed start-up session will be conducted at the Murdoch Childrens Research Institute on the same day as the MRI scan, and families will be given the computer to take home after the session.

During the Cogmed the start-up session, the Cogmed coach will explain how the training program works and will teach both the child and caregivers how to log into the system and complete training. The coach will also discuss planning and structuring the training with the child and their caregivers. Caregivers will also be given information on how to assist their child through the training program. Given that internet access is required for monitoring and recording the child’s progress, all families will be provided with (or reimbursed for) internet connection for the duration of the training period. Through a secure online server, the Cogmed coach will monitor the child’s training and compliance, which will be automatically captured by the training program itself. Program compliance will be assessed as the number of sessions completed by each child. The time spent per session will also be recorded. The Cogmed coach will contact families by phone each week to enquire about their progress and answer any questions from families regarding the program or the study.

### Procedures and measures

Study data will be collected via parent, teacher and self-report questionnaires, neuropsychological assessment focusing on working memory, attention and academic skills, and MRI. Table 1 outlines the study’s outcome measures and the time-points at which they will be collected.

**Table 1 T1:** **Outcome measures and study time**-**points**

**Outcome measures**			**Time-point**^**#**^			
			**Baseline***	**2 week**	**12 month**	**24 month**
**Academic achievement**	Wide Range Achievement Test-4th edition (WRAT-4)	Child	•	•	•	•
	Academic performance questionnaire	Parent	•	•	•	•
		Teacher	•			•
**Working memory**	Working Memory Test Battery for Children (WMTB-C)	Child	•	•	•	•
	Automated Working Memory Assessment (AWMA)	Child	•	•	•	•
**Attention**	Test of Everyday Attention for Children (TEACh)	Child	•	•	•	•
**Speed of processing**	CogState	Child	•	•	•	•
**General Cognitive ability**	Differential Ability Scale-2nd edition (DAS-II)	Child	•			
**Behaviour**	Strength & Difficulties Questionnaire (SDQ)	Parent	•	•	•	•
		Teacher	•			•
	Behavior Rating Inventory of Executive Function (BRIEF)	Parent	•	•	•	•
		Teacher	•			•
	Cogmed Training Evaluation Scales	Parent	•	•		
**Motivation**	Intrinsic Motivation Scale	Child	•			
	Intrinsic Motivation Inventory	Child		•		
**Neuroimaging**	MRI	Child	•	•		

^#^The presence of the ‘•’ symbol in Table 1 indicates when an outcome measure will be collected at a specific time-point from either a child or parent/teacher.

^*^Neuropsychological measures and behavioural questionnaires at the baseline time-point were completed prior to enrolment into the trial as part of a regional follow-up program.

#### Primary outcome

The primary outcome of the study is academic achievement 24 months’ post-intervention as measured using the Wide Range Achievement Test -4th edition (WRAT-4) [65]. The WRAT-4 includes subtests that assess reading (single word decoding), sentence comprehension, spelling, and math computation. Each scale is age standardised with a mean of 100 and SD of 15. Secondary information regarding literacy and numeracy, academic performance, grade repetition, and integration assistance will be sought from parents and teachers through an academic performance questionnaire.

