### Sample size

All 221 children from the VICS cohort will be invited to participate in the trial providing that they fit the eligibility criteria for this study. We conservatively estimate that approximately 60% of the VICS cohort will be eligible and will consent to participate in the trial, which will provide a sample size of 126 for this study (63 per treatment group; Figure 2). A participation rate of 60% allows for children who will not be seen through the VICS follow-up (10%), as well as children who do not meet the eligibility criteria (5%; approximately n= 11). A sample size of 63 in each group will enable us to detect an increase in our primary outcome, academic functioning (such as mathematics) 24 months' post-intervention, of 0.5 SD in the intervention compared with the placebo group, with 80% power and a type-I error rate of 5%. An increase of 0.5 SD in academic outcomes is the improvement seen following Cogmed in other populations after 6 months and would be a clinically important difference to detect [39]. Of the 126 participants, we expect approximately 80% to consent to the neuroimaging component of the study, thus a sample size of 100 (50 per group) to assess the secondary objective regarding neuroplasticity. A sample size of 50 in each group with neuroimaging data will enable us to detect differences of 0.57 SD in measures of neuroplasticity (i.e. percentage BOLD signal change between pre-intervention and 2-weeks’ post-intervention for fMRI analyses, and tract volume, FA or AD for DWI analyses), with 80% power and a type-I error rate of 5%.

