### Statistical analysis

All analyses will be carried out using an intention-to-treat approach, including all participants as randomised. Analysis will be carried out on those with outcome data available. Summaries of all primary and secondary outcomes will be presented by treatment group. Results will be presented as means and SDs of age standardised scores for continuous outcomes, and numbers and proportions for categorical variables. Differences between the groups on continuous outcomes will be assessed using linear regression adjusted for stratification factors of multiple births and low/normal working memory capacity at baseline. Models will be fitted using generalised estimating equations (GEEs) to allow for clustering of multiples, with results presented as the mean difference and 95% confidence intervals (CIs) calculated from sandwich estimates of standard errors. As a sensitivity analysis, results will also be adjusted for any other baseline factors where there is a chance imbalance between the 2 groups using linear regression. Differences between groups on binary outcomes will be assessed using logistic regression adjusted for stratification factors of multiple births and low/normal working memory capacity at baseline, again fitted using GEEs. Results will be presented as odds ratios (ORs) and 95% CIs calculated using sandwich estimates of standard errors. Due to the issues of multiple testing, results will be interpreted according to magnitude of the group difference rather than relying solely on significance levels. Compliance and motivation data will be presented descriptively by treatment arm.

For the fMRI data, the effects of group, time (pre-intervention and 2 weeks’ post-intervention) and task (0-back and 1-back conditions) will be examined using factorial analyses by fitting an analysis of variance (ANOVA) model [81]. fMRI effective connectivity will be examined using Dynamic Causal Modelling [82].

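### No single WRAT-4 score is designated as primary, so the stated 5% type-I error is not tied to one test of the primary outcome

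*Protocol article*

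**What the plan says.** Under Primary outcome, the protocol article gives one construct (academic achievement), one instrument (the WRAT-4) and one time point (24 months after the intervention). It then describes the instrument: "The WRAT-4 includes subtests that assess reading (single word decoding), sentence comprehension, spelling, and math computation". It adds: "Each scale is age standardised with a mean of 100 and SD of 15". That makes four separate scores. No total or composite is mentioned, and no subtest is put first. The study objectives and Table 1 are no more specific: they refer to academic functioning and to the WRAT-4 as a whole.

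Under Sample size, 63 children per group are said to be enough to "detect an increase in our primary outcome, academic functioning (such as mathematics) 24 months' post-intervention, of 0.5 SD" with 80% power and a 5% type-I error rate. Mathematics appears there as an example, not as the chosen variable.

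Under Statistical analysis, multiple testing is acknowledged, and the stated response is that "results will be interpreted according to magnitude of the group difference rather than relying solely on significance levels". No testing order, split of alpha or decision rule accompanies it.

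**The concern.** The 5% and the 80% belong to one test of one score, but the outcome they are attached to has four scores. As the text stands, any of the four could be presented as the primary result without departing from it.

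Reading by magnitude does not close the gap. If attention goes to the largest of several noisy differences, it goes to the one most likely to have been enlarged by chance.

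The Background section says that transfer from Cogmed to academic skills is disputed and that earlier findings were inconsistent. A single favourable subtest out of four, with the primary score not fixed beforehand, would leave that question where it was.

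**Working it through.** **Inputs from the protocol article.** 63 per group, 1:1 allocation, difference 0.5 SD, power 80%, type-I error 5% (Sample size and Randomisation); four subtests, each with its own standardised score (Primary outcome).

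**Assumed inputs.** The correlation r between subtest scores is not given, so a range of 0 to 0.9 is used, equal for all pairs. As in the plan's own calculation, clustering of multiples, covariate adjustment and dropout are ignored.

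**1. The plan's figure.** For two means with a two-sided test, n per group = 2(1.960 + 0.842)² / 0.5² = 62.8, so 63. Power at 63 per group is 80.1% by the normal approximation and 79.5% by the t distribution. A one-sided 5% test would need only 50. The stated figure is therefore one two-sided 5% test of one score, and it is correct for that.

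**2. Error if any of four subtests can support the claim.** With independent scores, the chance of at least one p < 0.05 under no effect is 1 − 0.95⁴ = 18.5%. For correlated scores it was simulated with four equally correlated z statistics (at least 1,000,000 draws per value of r). The last column counts only significant results in Cogmed's favour; the single-test figure is 2.5%.

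| Assumed r | At least one significant, either direction | At least one significantly favouring Cogmed |
|---|---|---|
| 0 | 18.5% | 9.6% |
| 0.5 | 15.6% | 7.8% |
| 0.6 | 14.4% | 7.2% |
| 0.8 | 11.4% | 5.7% |
| 0.9 | 9.3% | 4.7% |

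Both columns stay above their single-test values (5% and 2.5%) over the whole range.

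**3. Reading by magnitude.** The standard error of a difference is √(2/63) = 0.178 SD. Under no effect at r = 0.6, the largest absolute difference among the four averages 0.24 SD, and the largest in Cogmed's favour averages 0.12 SD. The chance that at least one subtest favours Cogmed by more than 0.3 SD is 12%.

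**4. Power if all four stay primary.**
- Bonferroni, 0.05/4 = 0.0125 each: power per subtest for 0.5 SD at 63 per group is 62% (normal) or 61% (t). The difference detectable with 80% power rises from 0.50 to (2.498 + 0.842) × 0.178 = 0.59 SD. Restoring 80% per subtest would need 90 per group, 180 in all.
- Holm, with a true 0.5 SD on all four: average power per subtest is about 69% (r = 0.9) to 73% (r = 0), by simulation.

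**5. Power if one score is primary.** Step 1 applies unchanged, provided that 0.5 SD is expressed in the SD of the chosen score.

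**The case against.** The strongest reply is that the article nowhere says four subtests will each be tested as primary. It defines one construct on one instrument at one time and then describes what the instrument contains. A reader might infer that the trial will run at an 18.5% false-positive rate, or that the 5% is simply wrong. The text does not support either reading. No rule says that any of four counts as success, 18.5% is only the upper end of a conditional range, and the 5% is right for the one comparison that was powered.

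A reader might also infer that multiplicity is ignored. It is not. The analysis section names the problem, says only that significance will not be relied on *solely*, and commits to mean differences with 95% confidence intervals and to summaries of all primary and secondary outcomes by group. That limits selective reporting, though it does not cap the type-I error.

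Finally, an analysis plan that is not shown may name the score, and testing order is commonly left to such a plan. This has force for the detail of a multiplicity procedure, and it is why no criticism is made here of how the secondary measures are ordered. It has less force for the identity of the primary variable. The article itself states the primary outcome, its error rate and its approach to multiplicity, and the three do not fit together.

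**Conclusion.** The concern holds in this form: the primary score is not designated, the 5% and 80% are stated for a single comparison, and the multiplicity rule offers no formal control. The consequence is conditional. If any of the four subtests at 5% may carry the primary claim, the two-sided family-wise error is about 9% to 18.5%. The chance of a significant subtest in Cogmed's favour is about 5% to 10%, roughly two to four times the 2.5% of a single test. Both ranges rest on assumed, equal correlations of 0.9 down to 0. The sample size arithmetic is sound. The point should be settled before unblinding because the confirmatory claim depends on it.

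**What to change.** Before unblinding, name one primary 24-month score and make the remaining WRAT-4 scores secondary. There are two ways to do this:

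- **A prespecified composite of the subtests**, with its construction written down. This keeps the stated construct of academic functioning.
- **One subtest.** This is simpler but narrows the objective. The sample size section does not already settle on Math Computation: it mentions mathematics as an example, and the Background reports the 0.5 SD gain for mathematical reasoning.

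Either way, 126 children, 80% power and 5% stand, with 0.5 SD read on the chosen score.

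If all four subtests must stay primary, state Holm's procedure for them in place of the magnitude rule and restate the power using the figures above.

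The cost is wording only. The downside is that a positive result on a non-primary subtest could no longer be claimed as the primary finding.

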#### Secondary outcomes

Working memory will be assessed using subtests from the Working Memory Test Battery for Children (WMTB-C) [63]. Verbal immediate memory will be assessed with the Digit Recall and Word List Recall subtests, which require the child to immediately recall verbal information. Visual-spatial immediate memory will be assessed with the Block Recall and Mazes Memory subtests whereby the child must immediately recall visual-spatial information. Verbal working memory will be assessed with the Backward Digit Recall subtest which requires the child to recall sequences of digits in the reverse order to that presented. In addition to the WMTB-C subtests, visual-spatial working memory will be assessed with Backward Block Recall, whereby the child must recall sequences of tapped blocks in the reverse order to that presented. A subtest from the Automated Working Memory Assessment (AWMA), known as Mister X, will also be used to assess visuo-spatial working memory [66].

Attention will be assessed using subtests from the Test of Everyday Attention for Children (TEACh) [67]: Sky Search (selective attention), Score! (sustained attention) and Creature Counting (shifting attention). Reaction time and decision making abilities (i.e. speed of processing) will be assessed using the Detection and Identification tasks from a computerised cognitive test battery (CogState Ltd, Melbourne, Australia). These tasks have been shown to be valid and reliable measures of speed of processing [68,69]. General cognitive ability will be assessed with the general cognitive ability score (GCA) from the Differential Ability Scale-2nd edition (DAS-II) [70]. The DAS-II is a well validated measure with excellent psychometric properties and is age standardised with a mean of 100 and SD of 15.

Behaviour will be evaluated using parent and teacher versions of the Strength & Difficulties Questionnaire (SDQ) [71]. The SDQ is a well-validated questionnaire that assesses overall behaviour problems, emotional symptoms, hyperactivity/inattention, peer relationship problems, and prosocial behaviour. Everyday manifestations of attention and working memory problems will be evaluated with the parent and teacher versions of the Behavior Rating Inventory of Executive Function (BRIEF) [72]. Parents will also be asked to complete a training evaluation scale prior to and following Cogmed training. This training evaluation is an integrated component of the Cogmed training model and seeks to gather information from parents regarding their child’s attention, hyperactivity and impulsivity.

In order to measure the child’s level of motivation and interest prior to, during, and after Cogmed training, several motivation questionnaires will be administered. Prior to commencing training, the Intrinsic Motivation Scale will be administered by the Cogmed coach to the child [73]. To assess motivation during the Cogmed training period, the Cogmed coach will ask the child a set of 7 questions concerned with how fun, motivating, and challenging the training has been for them. These questions will be asked after the first week of training, midway through the training and at the end of the training period. Following Cogmed training, a modified version of the Intrinsic Motivation Inventory (IMI) will be administered [74,75].

Neuroimaging pre-intervention and 2 weeks’ post-intervention will be performed using a Siemens 3 Tesla TIM Trio MRI scanner located at the Royal Children’s Hospital. A) High resolution structural sequences will be performed in order to transform MRI images into a common coordinate system for further functional and diffusion image analyses. The following sequences will be acquired: a) 3D T1-weighted (MPRAGE) with high resolution 0.8 mm^3^ isotropic voxels, and b) 3D T2-weighted with 0.9mm^3^ isotropic voxels. B) Diffusion-weighted imaging (DWI) sequences will be acquired with 2.3 mm^3^ isotropic voxels with 30 gradient directions at a b value of 1000 s/mm^2^, as well as 45 gradient directions at a b value of 3000 s/mm^2^. In addition, reversed phase-encode blip images will also be collected to correct for susceptibility distortions in the spin-echo DWI images [76]. Standard diffusion metrics will be obtained by applying the diffusion tensor model to the low value DWI data (b=1000). Probabilistic tractography will be conducted using constrained spherical deconvolution on the high value DWI data (b=3000) [77]. White matter fibre tracts previously shown to relate to working memory will be identified, including the superior longitudinal fasciculus and cingulum bundle [48,59]. Tract volume and measures of axonal density (fractional anisotropy (FA) and axial diffusivity (AD)) will be extracted from within these tracts of interest. C) Functional MR echo planar images will be acquired while participant complete an established working memory task (n-back); TR=2400ms, 3.3 mm^3^ isotropic voxels. The n-back task is a well-established working memory paradigm, in which participants are asked to look at a sequence of stimuli presented and indicate for each presented stimuli, if they remember seeing it previously [78,79]. The task will comprise of 1 conditions: 1) 0-back condition and 2) 1-back condition. In the 0-back condition, children will be asked to respond if a pre-specified letter (“X”) appears on the screen, while in the 1-back condition children will respond when the letter presented on the screen is the same as the letter presented immediately before (e.g. A S D F F; Figure 1). A low-level baseline condition will also be included in which the participant simply has to look at a white cross on the screen. In total, the task will take approximately 10 minutes to complete. Similar n-back tasks have been used successfully with school-aged children in fMRI studies and reported activation of prefrontal and parietal regions associated with working memory [80,81]. In addition, resting-state fMRI data (10 minutes) will also be acquired. Participants will be asked to lie still with their eyes closed. Previous research has found that resting-state fMRI is effective for assessing large-scale brain networks in children [82,83].

**Figure 1 F1:**
[figure not shown]
A schematic example of the A) 0-back and B) 1-back conditions of the n-back task.

Children will be carefully instructed about the imaging process prior to the MRI scan, and will have the opportunity to practice the fMRI task during a simulated ‘mock’ MRI session, which will occur prior to the scan on the same day. This preparation process will be conducted by experienced research staff and allows children to familiarise themselves with the scanner and scanning process, and raise any concerns they may have prior to the MRI scan. Furthermore, this process assists with identifying children who are unlikely to comply with the MRI procedure and is important for the acquisition of good quality MRI images without the use of sedation.

